**PART - C**

**Project Title: Association of ABO blood groups with presentation and outcomes of confirmed SARS CoV-2 infection: A prospective study in the largest COVID-19 dedicated hospital in Bangladesh**

**Summary**:

Since December 2019 COVID-19 is dominating the life of the people of this universe. Its behavior also varied among the nations of the universe. The risk factor of adverse outcome of COVID-19 was determined. No biologic markers for the susceptibility of the infection is yet to be found. The relation of blood group and infection was found in several disease like cholera, severe malaria, severity of dengue, H-pylori infection have been elucidated. Genome wide Association Study of Severe Covid-19 with Respiratory Failure, GWAS Group detected cross-replicating associations with rs11385942 at locus 3p21.31 and with rs657152 at locus 9q34.2. The association signal at locus 9q34.2 coincided with the ABO blood group locus. Several studies also found some contradicting results in this regard.

So to observe the impact of ABO blood groups on the presentation and outcome of Confirmed COVID -19 infection, this study was conducted in the largest COVID19 dedicated hospital in Bangladesh. It would be a prospective cohort study. A cohort of the patients with RT-PCR positive COVID-19 patients since June 2020 till September 2020 will be included in this cohort. Their blood group will be determined. The clinical features, severity, time required to recover, conversion of severity, Persistence of RT-PCR positivity 14 days after initial positivity will be determined. They will be followed up for at least 30 days or hospital discharge which one is longer. Comparison will be made in different blood groups.

The primary outcome would be the duration required to have clinical improvement.

Data will be analyzed using SPSS 20. To compare the groups one way ANOVA was done for continuous variable, Chi square for categorical variables. For outcome assessment relative risk (RR) with 95% CI was measured for qualitative variable categorizing blood group A and non A. survival analysis by Kaplan-Meier curve was done for the duration of recovery. Result of the study and statistical analysis will be presented by tables, figures, graphs, diagrams, charts and photographs. All these will have own legends (i.e. title) and will be serially numbered. Discussion will be done on the basis of result obtained from the study and comparing with similar studies done at home and abroad. Summarization will be drawn after discussion. Conclusion will be drawn depending upon the results and discussion.

**PART - D**

**Introduction:**

WHO (World Health Organization) first notify about the emergence of COVID-19 infection in Wuhan city, China in Late December^1^. Soon the novel virus became pandemic, declared on 12 March 2020^2^. On 19 September 2020, there have been 30,369,778 confirmed cases of COVID-19, including 948795 deaths reported to WHO^3^. The presentation of COVID-19 varied widely. The most common symptoms of COVID-19 involved fatigue, fever, dry cough, respiratory distress, anosmia and so on. A large proportion of the patient remains Asymptomatic as well^4^. Its behavior also varied among the nations of the universe. Genome wide Association Study on Severe Covid-19 with Respiratory Failure, GWAS Group detected cross-replicating associations with rs11385942 at locus 3p21.31 and with rs657152 at locus 9q34.2. The association signal at locus 9q34.2 coincided with the ABO blood group locus. They found a higher risk among persons with blood group A than with other blood groups^5^.Some other viruses like HBV^6^, SARS-COV^7^, and MERS-COV^8^ have susceptibility relation with ABO blood group. The mechanisms behind the impact of blood group are still unclear. Histo-blood group antigens are also expressed on endothelial cells (EC) and platelets^9^. SARS-CoV enter into human body through the replication in epithelial cells of the respiratory and digestive tracts. They have the ability to synthesize ABH carbohydrate epitopes. It has been hypothesized that the S protein of virions produced by either A or B individuals could be decorated with A or B carbohydrate epitopes, respectively. Guillon et al^10^. Reported that interaction between S protein and ACE-2 is specifically inhibited by human natural anti-A antibodies. SARS-COV and SARS-COV-2 have similar nucleic acid sequence and similar receptor combination with angiotensin-converting enzyme 2 (ACE2)^11^. It was also found that non-A type is a risk factor for venous thromboembolism, which is one of the pathogenesis for COVID-19 death^12^. But different studies showed contradicting results in relation to influence of blood group on susceptibility and outcome of COVID-19 infection^13, 14, 15, 16^. So to observe the impact of ABO blood groups on the presentation and outcome of Confirmed COVID -19 infection, this study was conducted in the largest COVID19 dedicated hospital in Bangladesh.

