**2. OBJECTIVES:**

**General objectives:**

To observe the association of different blood groups on presentation and outcome of confirmed COVID-19 infection.

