**Inclusion Criteria:**

- At least 18 years of age
- COVID-19 infection, confirmed by polymerase chain reaction (PCR) test
- Mild to moderate COVID-19 infection

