**Uncomplicated (mild) Illness**

These patients usually present with symptoms of an upper respiratory tract viral infection, including mild fever, cough (dry), sore throat, nasal congestion, malaise, headache, muscle pain, or malaise. Signs and symptoms of a more serious disease, such as dyspnea, are not present.

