**Clinical Feature**

| Trait |  | Follow-up  Yes-1, No-2 | | | | | | | | | | | | |
| --- | --- | --- | --- | --- | --- | --- | --- | --- | --- | --- | --- | --- | --- | --- |
|  | On Admission | D2 | D3 | D4 | D-5 | D-6 | D-7 | D-8 | D-9 | D-10 | D-11 | D-12 | D-13 | D-14 |
| Fever | Yes No |  |  |  |  |  |  |  |  |  |  |  |  |  |
| Cough | Yes No |  |  |  |  |  |  |  |  |  |  |  |  |  |
| Running nose | Yes No |  |  |  |  |  |  |  |  |  |  |  |  |  |
| Sputum | Yes No |  |  |  |  |  |  |  |  |  |  |  |  |  |
| Respiratory distress | Yes No |  |  |  |  |  |  |  |  |  |  |  |  |  |
| Sore throat | Yes No |  |  |  |  |  |  |  |  |  |  |  |  |  |
| Hoarseness of voice | Yes No |  |  |  |  |  |  |  |  |  |  |  |  |  |
| Chest pain | Yes No |  |  |  |  |  |  |  |  |  |  |  |  |  |
| Diarrhoea | Yes No |  |  |  |  |  |  |  |  |  |  |  |  |  |
| Vomiting | Yes No |  |  |  |  |  |  |  |  |  |  |  |  |  |
| Anosmia | Yes No |  |  |  |  |  |  |  |  |  |  |  |  |  |
| Anorexia | Yes No |  |  |  |  |  |  |  |  |  |  |  |  |  |
| Headache | Yes No |  |  |  |  |  |  |  |  |  |  |  |  |  |
| Confusion | Yes No |  |  |  |  |  |  |  |  |  |  |  |  |  |

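### The symptom grids have no row for fatigue, malaise or muscle pain, so the comparison of presentation by blood group would omit symptoms that the protocol itself names

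*Protocol*

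**What the plan says.** The general objective (Protocol, Objectives) is: "To observe the association of different blood groups on presentation and outcome of confirmed COVID-19 infection". The title pairs presentation with outcomes in the same way, and specific objective 2 names presentation again. The Summary makes clinical features a study variable to be compared between blood groups: "The clinical features, severity, time required to recover, conversion of severity, Persistence of RT-PCR positivity 14 days after initial positivity will be determined".

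Two places say which symptoms the authors regard as typical. The Introduction: "The most common symptoms of COVID-19 involved fatigue, fever, dry cough, respiratory distress, anosmia and so on". The operational definition of uncomplicated (mild) illness describes an upper respiratory infection, "including mild fever, cough (dry), sore throat, nasal congestion, malaise, headache, muscle pain, or malaise". Enrolment is restricted to "Mild to moderate COVID-19 infection".

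Research instruments lists only the consent form and the Case Record Form. On that form, the Clinical Feature grid (admission to D-14) and the Subsequent follow up grid (D-15 to D-30) share one fixed list of symptoms, each to be marked Yes or No.

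**The concern.** A study of presentation needs its form to collect the features that it treats as typical of the disease. Here the form and the protocol's own text do not match. The grids find room for items such as "Hoarseness of voice" and confusion, which neither the Introduction nor the mild-illness definition names. They have no row for three complaints that those sections do name.

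What is at stake is the descriptive comparison of presentation across blood groups. The omission bears most on mild patients, because it is the mild definition that mentions malaise and muscle pain. No later analysis plan can repair this, since it cannot analyse a variable that was never collected.

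**Working it through.** The protocol gives no figure to reproduce, so the check compares lists.

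**Grid rows (14, identical in both grids).** Fever, cough, running nose, sputum, respiratory distress, sore throat, hoarseness, chest pain, diarrhoea, vomiting, anosmia, anorexia, headache, confusion. There is no row for other symptoms.

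**Introduction against the grid (5 symptoms).**

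| Named symptom | Row on grid |
| --- | --- |
| Fatigue | none |
| Fever | yes |
| Dry cough | yes, as cough |
| Respiratory distress | yes |
| Anosmia | yes |

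Four of five are captured; fatigue is not.

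**Mild-illness definition against the grid (7 distinct features; malaise is printed twice).**

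| Named feature | Row on grid |
| --- | --- |
| Mild fever | yes |
| Dry cough | yes, as cough |
| Sore throat | yes |
| Nasal congestion | near equivalent: running nose |
| Malaise | none |
| Headache | yes |
| Muscle pain | none |

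Five of seven are captured, counting running nose; malaise and muscle pain are not.

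**Other pages of the form.** Demography holds the date on which symptoms started, but not which symptoms. The observation pages hold vital signs, oxygen saturation and comorbidity. The investigations page holds laboratory values, ECG and RT-PCR, and the imaging page holds radiology. The only open symptom field is an undated line for post-COVID symptoms, which concerns a later outcome and not presentation.

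**What depends on the missing rows.** The clinical improvement criteria, which define the primary outcome, use temperature, respiratory symptoms, imaging, comorbidity or complications, and oxygen saturation. None of the three missing symptoms appears there, nor in the definitions of moderate pneumonia, severe pneumonia or ARDS. The loss is therefore confined to the description and comparison of presenting and day-by-day symptoms.

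**Illustration of what a row could have shown (assumed inputs).** The protocol gives no symptom frequencies. Take the 400 cases of the ethics abstract at the 1:2 ratio of the sample size section: 400/3 gives about 133 group A and 267 non-A. Assume prevalence p0 in non-A and p1 = p0 + 0.15 in A, with a two-sided 5% test. With p the pooled proportion:

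- SE0 = sqrt(p(1 − p)(1/133 + 1/267)) and SE1 = sqrt(p1(1 − p1)/133 + p0(1 − p0)/267)
- Power = Φ((0.15 − 1.96 × SE0)/SE1)
- For 30% against 45%: p = 0.350, SE0 = 0.0506, SE1 = 0.0515, so the argument is 0.99 and power is about 84%
- For 40% against 55%: about 81%
- For 50% against 65%: about 82%

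So if the symptom were that common and the difference that large, the study could have detected it. The figures show scale only; the finding does not rest on them.

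**The case against.** The strongest reply is that neither source passage promises data collection. The Introduction is background and its list is open-ended. The mild definition is illustrative and is bounded by the absence of dyspnoea, for which the form has a respiratory distress row. Which symptoms go on a checklist is partly a matter of preference, and presentation is wider than the grid, since vital signs, laboratory values and imaging are also recorded. This limits the size of the point but does not remove it: the protocol names these symptoms as typical, makes presentation an objective, and gives no place to record them at admission.

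Some stronger readings are tempting and are not supported:

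- **That patients with only these complaints are classified as symptom-free.** The onset date on the Demography page would show that they had symptoms, and the protocol defines no asymptomatic category to be compared by blood group. How many such patients there would be is unknown.
- **That the presentation table would be wrong.** The 14 entries can be correct as far as they go; the table would be incomplete.
- **That the protocol ranks fatigue first.** It appears first in a sentence that gives no ranking.
- **That post-COVID capture fails.** The open line invites such complaints. What is missing is a structured daily record.
- **That the primary outcome is compromised.** The improvement criteria do not use these symptoms.

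**Conclusion.** The point holds in a limited form. The form cannot record fatigue, malaise or muscle pain as presenting or daily symptoms, although the protocol names all three, so the comparison of presentation by blood group would omit them. A patient with only these complaints would show No in all 14 rows, with only the onset date as evidence of symptoms.

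The effect falls on a stated objective but is descriptive. The primary outcome and the severity classes above mild are unaffected. The share of patients concerned cannot be given, because the protocol states no symptom frequencies; the power figures rest on assumed prevalences of 30 to 50% and an assumed 15-point difference. The conclusion itself needs only the lists in the protocol and its form. The change is worth making because it is cheap and because unrecorded follow-up days may not be recoverable later.

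**What to change.** Add two Yes/No rows, fatigue/malaise and muscle pain, to both the Clinical Feature grid and the Subsequent follow up grid, covering admission to D-30.

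For patients already enrolled, complete the admission entry from the indoor hospital records, which the ethics abstract already allows. Code anything undocumented as missing, not as No. Records are unlikely to supply daily entries to D-30, so retrospective completion should be limited to admission.

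Where the data cannot be obtained, state in the report that presentation is limited to the 14 listed symptoms.

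The cost is two more rows per visit, and missing values for patients enrolled before the change. That share may be large: the Introduction cites case counts of 19 September 2020, while the ethics abstract plans enrolment from June to August and the Summary allows inclusion until September 2020. If most patients were already enrolled when this text was written, the reporting statement may be the main remedy left.

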**2. OBJECTIVES:**

**General objectives:**

To observe the association of different blood groups on presentation and outcome of confirmed COVID-19 infection.

**Specific objectives:**

1. To observe the blood groups of the patients with COVID-19 infection.
2. To observe presentation and different outcome of the patients with confirmed COVID-19 infection.
3. To observe the differences in different blood groups.

**3. RATIONALE:**

Covid-19 is an emergent pandemic, threatens the life of millions of the people throughout the globe. The severity, outcome and susceptibility varies among the nations, race and individuals. Biologic markers of COVID-19 infection is still uncertain. Several studies revealed blood group A is most susceptible. The studies were performed with the affected patients only. This study Aim to observe the impact of different blood groups on presentation and outcome of confirmed COVID-19 infection. It would help us to detect a biologic marker for the susceptibility and outcome of COVID-19 infection.

1. **METHODOLOGY:**

Study type: Prospective cohort

Sample size:

Proportions to cure from COVID-19 by day-12 in group-1(blood group A) and group-2 (blood group Assuming expected B, O, AB) are 0.70 and 0.90 respectively. Thus we need a total of 378 samples at 1:2 ratio, and, that would provide a power of at least 90% at two tailed test where p value less than 0.05 to detect significant difference between the groups. Considering 10% dropout, we need 416 samples in total.

$$n=\frac{r+1}{r}\frac{p^{*}\left( 1-p^{*} \right){(Z_{\beta}+Z_{\frac{\alpha}{2}})}^{2}}{{{(p}_{1}- p_{2})}^{2}}$$

r = ratio of group-1 and group - 2

p*= Average of proportion

Z_α/2_ = Level of significance

Z_β_ = Power of the test

p_1_ - p_2_= Effect size

p_1_ = Proportion in group - 1

p_2_ = Proportion in group - 2

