**Abstract summary for Ethical Committee**

This hospital based Experimental study will be carried out in COVID-19 Unit, Dhaka Medical College Hospital for the duration of 4 months. Consecutive confirmed COVID-19 patients with mild to moderate severity whom will be enrolled from June, 2000 to august, 2000. Total 400 cases will be enrolled for the research. They will be followed up for at least 30 days or hospital discharge which one is longer.

1. By the following under mentioned steps confidentially will be maintained:

- Research data will be coded
- Data will be stored in a locked cabinets
- Only research personnel will be allowed to access data
- There is no physical, psychological, social and legal risk during physical examination. Proper consent will be taken.
- For safeguarding confidentially and protecting anonymity each of the patient will be given and ID no.
- A signed informed consent will be taken from the patient/patients guardians convincing that privacy of the patient will be maintained and he/she will not be compensated for loss of work time if they want.
- A data should (enclosed) be prepared for which a short interview of 15-30 minutes will be required
- Use of hospital records (indoor) will be needed to fill up the patients’ data sheet.

2. Consent form will be a written statement

1. A brief interview regarding study variables will be collected from the participants.

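### The stated sample size of 378 is twice what the protocol's own formula and inputs give (about 189), and the ethics abstract gives a different enrolment total (400 against 416)

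*Protocol*

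**What the plan says.** The sample size paragraph appears twice in the Protocol in the same words: under Methodology (within section 3, Rationale) and again under Methodology in Part-G, the abstract for the national ethics committee. It compares the proportions cured by day 12 in blood group A and in groups B, O and AB combined, which "are 0.70 and 0.90 respectively". The test is a "two tailed test where p value less than 0.05". The conclusion is "Thus we need a total of 378 samples at 1:2 ratio, and, that would provide a power of at least 90" per cent.

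A formula for n follows, with a list of symbols. One entry is "r = ratio of group-1 and group - 2", and p* is described as the average of the proportions. The list does not define n, so the reader is not told which group it sizes.

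On dropout the paragraph adds: "Considering 10% dropout, we need 416 samples in total". The abstract summary for the ethical committee gives another total: "Total 400 cases will be enrolled for the research".

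**The concern.** The paragraph prints its inputs, its formula and its result, so the result can be checked directly, and it does not follow from the inputs. An ethics committee reads this paragraph as the reason for the number of patients asked to take part. Here that number is presented as needed, although the stated assumptions support only half of it.

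The document also gives two totals for the same enrolment. Nothing in it says which one governs, and the smaller one, after the protocol's own dropout allowance, falls below the evaluable number that the protocol says it needs.

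**Working it through.** **Inputs, all from the sample size paragraph.** p1 = 0.70 (group A) and p2 = 0.90 (other groups), so the difference is 0.20. p* = (0.70 + 0.90)/2 = 0.80. Two-sided 5% gives z = 1.960 and 90% power gives z = 1.2816. The split is 1:2.

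**Formula as printed.** n = ((r+1)/r) × p*(1−p*) × (Zβ + Zα/2)² / (p1−p2)². Here (1.2816 + 1.960)² = 10.507, and 0.80 × 0.20 × 10.507 / 0.04 = 42.03.

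**Reproducing 378.** Reading r literally as group 1 over group 2 gives r = 0.5 and n = (1.5/0.5) × 42.03 = 126.09. Multiplying by 3 gives 378.3. The stated total therefore appears if 126 is taken as the smaller group: 126 + 252 = 378.

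**Which group does 126 size?** The formula rests on the condition p*(1−p*)(1/n1 + 1/n2) = (p1−p2)²/(Zβ + Zα/2)², and the right side is 0.04/10.507 = 0.00381.
- Groups of 63 and 126: 0.16 × (1/63 + 1/126) = 0.00381. The condition is met.
- Groups of 126 and 252: 0.16 × (1/126 + 1/252) = 0.00190. This is half the variance required.

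So with r = 0.5 the formula returns the larger group.

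**Correct totals.**
- r = 0.5: larger group 126.09, smaller group 63.04, total 189.1.
- r = 2: n = (3/2) × 42.03 = 63.04 for the smaller group, larger group 126.09, total 189.1.
- Rounding the smaller group up: 64 + 128 = 192.
- Ratio of stated to computed: 378/189 = 2.0.

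**Other standard variants (two-sided 5%, 90% power, 1:2).** The pooled-variance formula gives 60 + 120 = 180. With a continuity correction it gives 67 + 134 = 201. The printed formula with p* weighted 1:2 (0.833) gives 164. None is near 378.

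**Power for 0.70 against 0.90 (normal approximation).**

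| Groups | Pooled variance under the null | Unpooled variance |
|---|---|---|
| 63 : 126 | 91.5% | 88.2% |
| 126 : 252 | 99.6% | 99.4% |

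For 126 : 252, the standard error under the null is √(0.8333 × 0.1667 × (1/126 + 1/252)) = 0.0407, and under the alternative √(0.21/126 + 0.09/252) = 0.0450. Pooled: (0.20 − 1.960 × 0.0407)/0.0450 ≈ 2.67, which gives 99.6%. Unpooled: 0.20/0.0450 − 1.960 ≈ 2.49, which gives 99.4%.

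**What 378 could detect.** At 126 : 252, 0.77 against 0.90 has 90.5% power by the pooled approximation.

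**Enrolment totals.** 378 × 1.10 = 415.8, hence 416. After 10% loss, 416 leaves 374 and 400 leaves 360. The gap between the two totals is 16 patients, or 16/416 = 3.8%.

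**The case against.** The strongest reply is that nothing is endangered. The protocol states a floor for power, and 126 : 252 clears it easily. The methodology describes a prospective cohort, so extra patients cost data collection and do not receive an assigned treatment. Even 400 enrolled, with 10% lost and split 120 : 240, gives 99.5% power (pooled). All of this stands, and it limits the consequence. It does not rescue the sentence that 378 are needed, nor does it reconcile 400 with 416.

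Some stronger readings are tempting but not supported:
- **The power is misstated, or the study is underpowered.** At least 90% is literally true at about 99%. The protocol also states no detectable difference for 378 other than the 20 points it assumes.
- **A null result would mislead.** Greater precision makes a null result more informative, and the data analysis section plans relative risks with 95% confidence intervals, which show it.
- **The dropout step is a second error.** 416 is 378 with the common shortcut of adding 10%, so it is meant to differ from 378. Dividing by 0.9 gives 420, a difference of 4 patients or about 1%. That is a minor imprecision.
- **The cause is known.** The product 126 × 3 fits exactly, but the protocol neither defines n nor shows which r was entered, so this remains an inference.
- **189 guarantees 90% power.** It is what the printed formula gives. By other approximations the power is 91.5% or 88.2%.

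**Conclusion.** The concern holds as a correction of figures. The printed formula with the stated inputs gives about 189 in total (192 rounded up), and the stated 378 is twice that. The most likely explanation is that the larger group's size was used as the smaller group's. The error is towards too many patients; no analysis or conclusion is invalidated.

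Separately, 416 in the two methodology sections and 400 in the ethics abstract are conflicting figures for one quantity.

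The total of 189 rests on p* being the simple average, 0.80. The power figures rest on the 1:2 split holding, which consecutive sampling does not control.

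**What to change.** In both copies of the sample size paragraph:

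1. Define n as the size of a named group and state the direction of r.
2. State that the formula gives about 63 + 126 = 189 (64 + 128 = 192 rounded up) for 0.70 against 0.90.
3. If about 378 evaluable patients are kept, remove the claim that this number is needed for 90% power. Say what it delivers if the split is 1:2: about 99% power for 0.70 against 0.90 (99.6% pooled, 99.4% unpooled), or about 90% power for roughly 0.77 against 0.90 by the pooled approximation.

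Then use one enrolment figure in both methodology sections and in the abstract for the ethical committee: for example 416, noting that it leaves about 374 after 10% loss, or 400, noting that it leaves 360.

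The cost is rewording and restated figures. Neither option goes above the 416 already in the protocol, though choosing 416 raises the ethics abstract's figure by 16.
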